#### Training and education of the trial occupational therapists

All occupational therapists of the two intervention groups in the nursing homes will receive information about the study, including a manual with the procedures and a two-day training session (first day before the start of OTc and the second day before the start of OTcsm) regarding how to make use of the CBT principles in coaching the participant and how to make use of the SO-HIP tool in instructing and coaching the patient (face to face and by telephone), following the five steps of CBT. Along with the coaching on the use of the sensor data, the occupational therapists will be instructed about the technical aspects of the SO-HIP tool and the use of the web-based application. Details of the training program can be found at www.sohipstudie.nl. The occupational therapists are all registered, have a bachelor’s degree and have experience in the rehabilitation of patients after hip fracture.

### Use of co-interventions

Patients are allowed to receive concurrent interventions during the study period (e.g., medications, dietician). Details of the concurrent intervention(s) will be registered.

### Outcome and measurements

Table 3 gives a detailed overview of outcome measures at each time point.

**Table 3 Tab3:** Variables and outcome measures and time points of assessment in the SO-HIP study

Measures	Baseline NH1	T1 NH2	T3 H1	T6 H2
Primary outcome measure				
Daily functioning; self perceived performance in daily activities:				
o COPM	X	X	X	X
Secondary outcome measures				
Physical functioning;				
o Performance oriented mobility: POMA	X	X	X	X
o Functional mobility and balance: TUG	X	X	X	X
Independence in Activities of Daily Living (ADL) and Instrumental Activities of Daily Living (IADL;				
o Katz-15 index	X	X	X	X
Sense of safety;				
o VAS-SAFE	X	X	X	X
Fear of falling;				
o VAS-FOF	X	X	X	X
o FES-I	X	X	X	X
Health related quality of life;				
o EQ 5D	X	X	X	X
Additional measures				
Information gathered of determinants of functional decline (e.g., comorbidities) and a minimal data set (MDS) consisting of;				
o Demographic data,	X			
o Psychological and social functioning; subscale Rand 36	X	X	X	X
o Cognitive functioning; MMSE	X			X
o Healthcare utilization	X		X	X

Baseline, NH1 = within 1 week after admission nursing home; T1, NH2 = before discharge from nursing home; T3, H1 4 months (post-intervention) at home; T6, H2 = 6 months after the start rehabilitation. *COPM* Canadian Occupational Performance Measure, *POMA* Performance Oriented Mobility Assessment, *TUG* Timed Up and Go, *Katz 15 index* Modified Katz 15 index, *VAS-SAFE* Visual analogue scale for sense of safety, *VAS-FOF* Visual analogue scale for fear of falling, *FES-I* Falls Efficacy Scale International, *EQ5D* EuroQol health related quality of life, *MDS* Minimal Dataset, *MMSE* Mini Mental State Examination

### Medical and demographic variables

The self-reporting questionnaire that participants fill out at baseline and T4 contains determinants of functional decline (e.g. comorbidities) and the elements of a minimal data set (www.topics-mds.eu) consisting of demographic data (e.g. age, gender, marital status), physical functioning, self-perceived health status, psychological and social functioning, health-related quality of life and health care utilization.

### Primary outcome measure

The primary outcome measure is the perceived daily functioning 6 months after the start of rehabilitation compared to baseline functioning (the first week after admission). The primary outcome measure will be measured using the Canadian Occupational Performance Measure (COPM) [35]. The COPM is a client-centered, occupation-focused outcome measure for the detection of change in perceived occupational performance over time. It is a generic measure suitable for all clients with perceived problems in daily activities. It uses a semi-structured interview format and a structured scoring method. The COPM results in two main scores, Performance and Satisfaction, each out of total of 10. The patient prioritizes up to five problems s/he deems that are the most urgent or important and rates the problems on an ordinary 10-point scale regarding performance (1 = not able to do at all and 10 = able to do extremely well) and satisfaction (1 = not satisfied at all and 10 = extremely satisfied). The mean scores will be obtained by summing the ratings for performance and satisfaction and dividing them by the number of prioritized problems. Change in scores can be calculated after a reassessment interval to measure the change in the perception of occupational performance. For evaluation at a later time, the patient rates the performance regarding the prioritized problems outlined in the first interview. The COPM is a standardized instrument, with specific instructions and methods for administering and scoring. The reliability and validity of the COPM have been shown in many studies, and the COPM is widely used as an outcome measure for individuals and interventions [36–40]. A 1.3-point difference between pre- and post-measurement indicates a minimally clinically important difference [39, 40].

In this study, a trained research assistant will do the COPM interview and score the results.

### Secondary outcome measures

The secondary outcome measures are the level of physical activity and independence in activities of daily living, the level of sense of safety, fear of falling, self-rated health and the use of healthcare resources at 1, 4 and 6 months after start of the rehabilitation, compared to functioning at baseline at the beginning of rehabilitation in the nursing home.

*Physical functioning* will be measured based on the following:
*Performance oriented mobility* will be measured using the Tinetti Performance Oriented Mobility Assessment (POMA). The POMA is an easily administered, generic and widely used task-oriented test that measures the gait and balance abilities of older adults and their association with the risk of falling (high risk of falls (Tinetti score ≤18 points), moderate risk of falls (Tinetti score between 19 and 23 points), and low risk of falls (Tinetti score ≥24 points) [41]. It is clinically used to determine the mobility status of older adults or to evaluate changes over time. The POMA score ranges from 0 to 28, with a higher score indicating better balance and walking ability [41]. The inter-rater and test–retest reliability of the POMA is excellent, and the correlation with reference performance tests indicates the satisfactory construct validity of the POMA [42].
*Functional mobility and balance* will be measured by the Timed Up and Go (TUG). The amount of time to rise from a chair with arm rests, walk 3 meters, cross a line on the floor, turn, walk back, and sit down again will be measured [43]. The test will be performed twice, and the mean time will be used as the outcome [44]. The TUG range for people aged 80 to 99 years expressed as the mean has been estimated to be 11.3 ((95% confidence interval10.0-12.7) seconds [45] and 11 to 20 s in frail elderly and disabled patients [43]. The TUG is well validated and has been used in several studies on hip fracture patients to predict falls, to assess functional mobility and to assess the effects of home-based therapy and comprehensive geriatric care [3, 43, 46–48].
*Independence in Activities of Daily Living (ADL) and Instrumental Activities of Daily Living (IADL)* will be measured using the modified Katz-ADL 15 index score. This index is based on six basic ADLs and nine IADL items. Each item is scored 0 (independent) or 1 (dependent), with an overall score ranging from zero to 15; a higher score indicates a higher dependence in ADL and IADL [49, 50].

#### Sense of safety

The visual analogue scale for sense of safety (VAS-SAFE) will be used to measure sense of safety levels. The respondents answer the question “How safe do you feel at home?” The participants are instructed to select the number that best reflects their perceived sense of safety, with 1 representing feeling safe and 10 representing feeling extremely unsafe.

*Fear of falling* will be measured with the visual analogue scale for fear of falling (VAS-FOF) and the Falls Efficacy Scale International (FES-I).The VAS-FOF is a simple and easy-to-use instrument that uses a numeric scale (1–10) to measure the perceived FOF. The participants are instructed to select the number that best reflects the intensity of FOF experienced, with 1 representing no FOF and 10 representing an extreme FOF [51].The Falls Efficacy Scale-International (FES-I) is a short, easy-to-administer tool that measures the level of fear of falling during social and physical activities inside and outside the home, whether or not the person actually does the activity. The level of concern is measured on a four-point Likert scale (1 = not at all concerned to 4 = very concerned) [52].

The reliability and structural validity of the FES-I in patients after a hip fracture are good [53]. The Falls Efficacy Scale-International (FES-I) is commonly used to the measure fear of falling in community-dwelling older adults but can also be used to assess the fear of falling in patients after hip fracture [38].

#### Health-related quality of life

Self-reported health-related quality of life will be measured with the EQ 5D (EuroQol), comprising a visual analogue scale (VAS) and a health status instrument. EQ-5D is a validated, generalized and standardized instrument for use as a measure of health outcome. The EQ 5d compromises the following 5 dimensions: mobility, self-care, activities, pain/ discomfort and anxiety/depression, and one question about cognition. Each dimension has three levels: no problems, some problems or extreme problems [54]. A respondent’s EQ-VAS indicates self-rated health on a scale in which the endpoints are labeled ‘best imaginable health state’ (100) and ‘worst imaginable health state’ (0).

It was found that the EQ-5D could be used to measure outcomes for patients recovering from hip fracture, including those with cognitive impairment [55].

### Process evaluation

In addition to the primary and secondary outcomes, additional qualitative data will be collected, which will give insight into the feasibility of the SO-HIP tool at the level of both the older participants after hip fracture and the professionals using this intervention. Participants’ experiences and opinions with the standard care, OTc and OTcsm will be evaluated in a qualitative study, which will be done alongside the feasibility study of the SO-HIP study. From the professionals we will collect data using standardized evaluation forms. For each participant, each therapist will record the content of their intervention, the number of sessions, time spent and their views of effectiveness of the intervention. At the end of the study we will conduct a focus group with all professionals involved in the study exploring their experiences and opinions regarding the use of coaching and the use of coaching combined with sensor monitoring.

### Sample size calculation

Stepped wedge designs with more than two interventions have, to our knowledge, never been reported. The methodology for sample size and power calculations are still being developed. [name], PhD (Biostatistics, Radboud University Medical Center) performed a simulation-based power calculation based on the primary outcome – the COPM performance outcome. Specifically, with 8 patients per cluster (nursing home) per step (six steps of 2 months duration each), an assumed treatment effect 1 (occupational therapy without sensor monitoring (OTc) versus usual care (control, C) of 1.5*SD) and an assumed treatment effect 2 (occupational therapy with sensor monitoring (OTcsm) versus OTc of 0.75*SD), and an intracluster correlation coefficient of 0.05, we will collect observations on 288 patients and achieve a power of 100% for treatment effect 1 and a power of 85% for treatment effect 2. We expressed the treatment effect sizes relative to the standard deviations (SD) because similar data are currently lacking.

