**Methods/ Design:**

Six nursing homes will be randomized in a three-arm stepped wedge cluster randomized trial. All nursing homes will initially provide standard care. At designated time points, nursing homes, successively and in random order, will cross over to the provision of OT and at the next time point, to sensor monitoring-enhanced OT. A total of 288 older individuals, previously living alone in the community, who after a hip fracture were admitted to a geriatric rehabilitation ward for a short-term rehabilitation, will be enrolled.

Individuals in the first intervention group (OTc) will participate in an OT rehabilitation program with coaching based on cognitive behavioral therapy (CBT) principles. In the sensor monitoring group, sensor monitoring is added to the OT intervention (OTcsm). Participants will receive a sensor monitoring system consisting of (i) an activity monitor during nursing home stay, (ii) a sensor monitoring system at home and a (iii) a web-based feedback application. These components will be embedded in the OT. The OT consists of a weekly session with an occupational therapist during the nursing home stay followed by four home visits and four telephone consultations. The primary outcome is patient-perceived daily functioning at 6 months, assessed using the Canadian Occupational Performance Measure (COPM).

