## Background

Each year in the Netherlands, 17,000 people are admitted to a hospital after a hip fracture. The effects of a hip fracture are serious; one year after a hip fracture, 25% of patients have died and 20–90% of older individuals have new Activities of Daily Living (ADL) disabilities, defined as a functional decline [1–3]. Risk factors for functional decline after hip fracture can be divided into non-modifiable and modifiable risk factors. Non-modifiable risk factors are older age, female gender, living alone, cognitive impairment (dementia) and comorbidities. The modifiable risk factors are activities of daily living (ADL), walking ability, and depression [4–6]. Psychological factors such as low levels of self-efficacy and fear of falling have also been associated with functional decline after hip fracture in older individuals [7, 8].

Currently, most multidisciplinary rehabilitation programs for patients after hip fracture concentrate on improving mobility and ADL function but not fear of falling [7]. The evidence on the effectiveness of these rehabilitation programs on the recovery of ADL function is mixed. Exercise interventions have been used to improve physical function (e.g., gait speed, mobilization, balance, and strength), but despite an improvement in physical function, many older persons do not achieve a full recovery of ADL function [9, 10]. High-intensity (e.g., 4 times a week physical therapy) and intensive extended supervised exercise programs (e.g., during 12 month) had a significant impact on various physical functions, but the cost-effectiveness of these extended programs is unclear [11]. The main component of effective studies is ‘home-based functional task exercises’ (e.g., walking stairs, transferring), which results in a modest improvement in physical function post-discharge or at one year after discharge [12].

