**Table 1 Tab1:**
[figure not shown]
Design of the three-phase stepped wedge cluster randomized trial

*C* Care as usual, *OTc* Occupational therapy with coaching, *OTcsm* Occupational therapy with coaching and sensor monitoring, *NH* = *Cluster* = Nursing home

Trial duration =12 months (recruitment), 18 months (including exposure and measurements

Number of clusters = 6. Number of groups =3. Number of clusters per group =2 (cross over simultaneously)

Pre-rollout period = 2 months. Rollout period = 8 months. Post-rollout period = 2 months

Step length (intervention 1-2) = 2 months. Number of participants per step = 8

Reporting following Copas et al 2015 (Trials, Fig. 1) [58]

Six clusters (nursing homes) will be randomized to one of three fixed sequences, each containing the three interventions. All clusters will start with providing standard care (control condition) at the beginning of the study. At predetermined time points, two clusters cross over from the control condition (C) to the first intervention, the OT intervention with coaching based on CBT (OTc). At other predetermined time points, two clusters crosses over to sensor monitoring embedded in an OT intervention based on CBT (OTcsm). The interval between the different time points will be 2 months. One advantage in terms of the willingness to participate applicability of the trial to the nursing homes is that all of the nursing homes will have implemented the intervention at the end of the study.

The feasibility study started October 20, 2015 with the Amaris Health group in two locations in Laren and Hilversum and will end September 2016. The methods and procedures are feasible. We made minor improvements to some of the procedures for the main study. The main study has started April 1, 2016 and will end September 2017. The following nursing homes, situated in the Northwest and Midwest part of the Netherlands, are involved in the main study: the Omring with locations in Hoorn and Lutjebroek, Magentazorg with locations in Alkmaar and Bergen, Amstelring with locations in Amstelveen and Hoofddorp, Zorgbalans with locations in Ijmuiden and Haarlem, Careyn with locations in Utrecht and Vinkeveen and Evean with a location in Zaandam and two locations in Amsterdam.

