### Randomization procedure

Randomization was performed, 4 weeks before the start of the study, by the second author, who was not involved in the day to day logistics of care delivery. A dedicated program was written using the sample command in Stata version 13.1 (Stata Corp LP, College Station, TX) applying the following principles: (i) centers were ranked as to their size and likely patient recruitment potential; (ii) three strata were formed, 2 largest, 2 intermediate-sized and the 2 smallest centers; (iii) these were allocated in a way that would enhance the likelihood of collecting similar amounts of information the 3 strata across the 6 time periods; (iv) in particular, we forced the intermediate-sized centers in the 2-2-2 months periods; (v) we randomized the remaining 4 centers such that 1 large and 1 small center followed the 1-2-3 months periods and the other pair the 3-2-1 months periods, respectively.

Figure 1 shows the flow of clusters and participants through the trial using an adapted CONSORT diagram [27].

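### The 85% power for the sensor contrast assumes a 6-month COPM from all 288 enrolled patients; with plausible loss it is modestly lower unless baseline adjustment makes up the difference

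*Protocol article*

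**What the plan says.** The abstract of the Protocol article gives the enrolment target: "A total of 288 older individuals, previously living alone in the community". The section Sample size calculation builds its simulation "with 8 patients per cluster (nursing home) per step (six steps of 2 months duration each", with an ICC of 0.05 and assumed effects of 1.5 SD (OTc versus control) and 0.75 SD (OTcsm versus OTc). It concludes that the trial will "collect observations on 288 patients and achieve a power of 100% for treatment effect 1 and a power of 85% for treatment effect 2". Under Study population/eligibility, each home must be able to enrol at least 48 patients, 8 per step.

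The Background reports that "one year after a hip fracture, 25% of patients have died". The primary outcome is a COPM interview 6 months after the start of rehabilitation. The Statistical analysis section specifies a linear mixed model with a random intercept per home and fixed time, and uses the baseline value of each outcome as a covariable. No section mentions an allowance for death, withdrawal or a missing 6-month interview.

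**The concern.** The number enrolled and the number observed are the same figure. A patient who has died or cannot be interviewed at 6 months gives no COPM score, and an intention-to-treat analysis does not supply one. With the mortality that the article itself cites, complete follow-up at 6 months is implausible, so the stated power belongs to a situation the trial is unlikely to meet.

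The contrast affected is OTcsm versus OTc. It is the question in the trial's title and the only one whose stated power is near the usual threshold. A null sensor result would be read against a power of 85%, which may be a few points too high.

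**Working it through.** **Inputs from the article.** The layout is "Number of clusters = 6. Number of groups =3. Number of clusters per group =2", with six two-month steps and 8 patients per home per step: 6 × 6 × 8 = 288. The eligibility minimum gives the same total, 6 × 48 = 288, so no surplus is built in. For the sequences, "we forced the intermediate-sized centers in the 2-2-2 months periods" and "1 large and 1 small center followed the 1-2-3 months periods and the other pair the 3-2-1 months periods". The content of Table 1 is not available, so I read these as numbers of two-month periods in control, OTc and OTcsm. ICC is 0.05. Two-sided 5% is taken from the two-sided 95% intervals in Statistical analysis.

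**Method.** Generalised least squares on the 36 home-by-step means, with six categorical step effects and two treatment dummies. For each home, V = (σ²/n)·I + τ²·J, where n is the number of observed patients per cell. The treatment variances come from (XᵀV⁻¹X)⁻¹, and power = Φ(effect/SE − 1.96). The article does not say which SD its effects refer to, so both readings are used:
- total SD: σ² = 0.95, τ² = 0.05
- residual SD: σ² = 1, τ² = 0.05/0.95

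**Reproducing the stated figure (n = 8).**
- Total SD: SE = 0.2387; 0.75/0.2387 − 1.96 = 1.18; power 88.2%.
- Residual SD: SE = 0.2449; 0.75/0.2449 − 1.96 = 1.10; power 86.5%.
- With a t reference on 28 df: 85.8% and 84.1%.
- OTc versus control at 1.5 SD: above 99.9%.

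Both stated powers are thus recovered at, or close to, full observation of 8 per cell.

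**Loss by 6 months (assumed).** The article gives one-year mortality only. Converted to 6 months, 25% becomes 25/2 = 12.5% if deaths accrue evenly, or 1 − √0.75 = 13.4% under a constant hazard. Loss d is modelled as n = 8(1 − d).

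The last column below starts from the stated 85%. That implies SE = 0.75/(1.96 + 1.036) = 0.2503, which is then inflated in the same ratio as the computed SE. At 12.5% loss: 0.2503 × 0.2535/0.2387 = 0.2658; 0.75/0.2658 − 1.96 = 0.86; power 80.5%.

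| Loss | Evaluable | Total SD: SE, power | Residual SD: SE, power | Scaled from 85% |
|---|---|---|---|---|
| 0% | 288 | 0.2387, 88.2% | 0.2449, 86.5% | 85.0% |
| 10% | 259 | 0.2503, 85.0% | 0.2568, 83.2% | 81.5% |
| 12.5% | 252 | 0.2535, 84.1% | 0.2601, 82.2% | 80.5% |
| 20% | 230 | 0.2639, 81.1% | 0.2708, 79.1% | 77.3% |
| 25% | 216 | 0.2717, 78.8% | 0.2788, 76.7% | 74.9% |

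At 13.4% loss (249 evaluable) the three powers are 83.8%, 81.9% and 80.2%. OTc versus control stays above 99.9% in every row.

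**Baseline covariate.** If baseline COPM has within-home correlation r with the outcome, σ² becomes σ²(1 − r²). Loss replaces n by n(1 − d). The two cancel when r² = d: r = √0.125 = 0.35 at 12.5% loss, √0.20 = 0.45 at 20%, and √0.25 = 0.50 at 25%. The article gives no value for r.

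**The case against.** The strongest case is that nothing has been miscalculated. The product is 288, the stated powers reproduce, and a journal article often leaves a dropout allowance to the full protocol. The 25% covers hip-fracture patients in general over a year, whereas this trial excludes terminal illness and patients awaiting permanent placement and measures at 6 months. The planned baseline adjustment is not mentioned in the power calculation and could recover all of the loss at a moderate correlation.

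Nor do the numbers alone rule out a built-in allowance. Under the total-SD reading, 85.0% is the power at 10% loss. A different layout (1-1-4, 2-1-3, 3-1-2) gives 89.4% with no loss and 85.3% at 12.5%.

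Most of this stands as a limit on size and certainty. It does not remove the point. The article prints its inputs and ties the result to 8 patients per step and to observations on the same 288 it will enrol, so its wording leaves no room for a hidden allowance. It also does not claim the covariate gain.

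Three stronger readings are tempting but unsupported:
- **That 85% certainly overstates the power the trial will have.** Because r is not given, the net direction after baseline adjustment is undetermined.
- **That power is inadequate at the clinically important difference.** The article's figure, "A 1.3-point difference between pre- and post-measurement indicates a minimally clinically important difference", is a change within a patient and not a difference between arms. Converting it to SD units needs a COPM SD that the article does not give; it says similar data are lacking.
- **That OTcsm versus control is unpowered because no figure is quoted.** The two assumed effects imply 1.5 + 0.75 = 2.25 SD. With an SE of 0.373 (total SD, no loss), power exceeds 99.9%, and it does so even at 25% loss.

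**Conclusion.** The point holds as one of moderate to minor weight. As written, the 85% for OTcsm versus OTc is a complete-follow-up figure, and the article's own mortality figure makes complete follow-up implausible. If loss by 6 months is about the mortality-only level (12.5 to 13.4%), power without baseline adjustment falls by about 4 to 5 points, to roughly 80–84%. At 25% total loss it falls by about 10 points, to roughly 75–79%. OTc versus control is unaffected.

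These figures rest on an assumed loss rate, on loss spread evenly over homes and steps, on the sequences as read from Randomization procedure, and on no gain from the baseline covariate. Design, analysis model and effect estimates are not in question. What changes is how a null sensor result should be read.

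**What to change.** In Sample size calculation, state whether 288 is the number enrolled or the number expected to provide a 6-month COPM. Rerun the existing simulation at a stated evaluable number per home and step, with the assumed loss rate given, and replace 85% with the resulting figure or range. On the calculation above, 216 to 252 evaluable patients would give about 75–84%. If the baseline covariate is relied on to offset loss, state the assumed baseline-outcome correlation and include it in the simulation.

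The cost is one rerun and one reworded paragraph, with a quoted power that may be slightly less favourable. Enrolment, design and analysis stay as they are.
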